#### Interim analyses {21b}

The Data Safety Monitoring Board (DSMB) will meet either in-person or remotely to discuss matters related to the safety of study participants, validity and integrity of the data, enrollment rate relative to expectations, characteristics of participants, retention of participants, adherence to the protocol (potential or real protocol deviations), and data completeness.

The DSMB will review the interim data from the study once a total of 20 subjects have been treated with either the study drug or standard-of-care for at least 3 months, and again when all subjects have completed their 6-month study treatment. The DSMB may review the safety data at other times as warranted by emerging results. Based on review of the safety data, the DSMB can recommend continuation of the study without modification(s), study interruption, study termination, or modification of the trial, where applicable.

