**Methods:**

The PREP-AF trial is a double-blind randomized controlled feasibility trial. Individuals undergoing major thoracic surgery who are identified to be high-risk by the POAF prediction model will be randomized 1:1 to receive a short course of amiodarone vs. placebo in the immediate postoperative period. The primary outcome is feasibility, which will be measured by the number of eligible patients identified, consented, and randomized; intervention adherence; and measurement of future outcomes of a full trial.

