### Interventions

#### Explanation for the choice of comparators {6b}

Placebo was selected as a comparator because no prophylactic agent is given as part of standard of care at our institution. In our survey of thoracic surgeons in Canada, only 5 of 67 respondents (7.4%) consider prophylaxis routinely.

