#### Intervention description {11a}

Eligible high-risk patients will be randomized 1:1 to two treatment arms: *Intervention* patients will undergo the following: (a) postoperative day (POD) 0: receive 1050mg of amiodarone in 500mL of 5% dextrose in water (D5W) administered intravenously (IV) initiated at the time of anesthesia induction over 24 h at a rate of 0.73mg/min (43.75ml/h); (b) POD 1 to 5 or day of discharge (whichever occurs first):
*◦ If able to tolerate po intake:* 400mg po BID for postoperative days 1 to 5 or until the day of discharge (whichever occurs first).*◦ If unable to tolerate po intake:* 1050mg IV in 500mL of 5% dextrose administered over 24h for postoperative days 1 to 5 or until the day of discharge (whichever occurs first).

*Control* patients will receive identically marked IV infusions or oral capsules, containing D5W or placebo. These dosing regimens, in keeping with published protocols, are considered safe in thoracic surgery patients [9, 11].

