#### Sample size {14}

No sample size calculation was conducted for this feasibility study. We aim to recruit 80 patients for randomization during this 12-month trial. Our institution conducts approximately 200 major thoracic surgeries annually and we anticipate 100 of those patients to be eligible for inclusion based on POAF risk and assume a recruitment rate of 80. Patients will follow the schedule activities described in the “Participant timeline {13}” section including a 30-day follow-up.

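### Both scheduled DSMB reviews wait for 3 and 6 months of study treatment, but treatment lasts at most 6 days, so neither review can fall due as written

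*Protocol article*

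**What the plan says.** Interim analyses {21b} schedules two DSMB reviews. The first is due "once a total of 20 subjects have been treated with either the study drug or standard-of-care for at least 3 months", and the DSMB looks "again when all subjects have completed their 6-month study treatment". The section adds: "The DSMB may review the safety data at other times as warranted by emerging results".

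The rest of the article describes a much shorter treatment:

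- The abstract calls it "a short course of amiodarone vs. placebo in the immediate postoperative period".
- Intervention description {11a} has the infusion "initiated at the time of anesthesia induction over 24 h", followed by "400mg po BID for postoperative days 1 to 5 or until the day of discharge (whichever occurs first", or a daily infusion over the same days if oral intake is not tolerated. Control patients follow the same schedule.
- Sample size {14} describes the activity schedule as "including a 30-day follow-up", and Adverse event reporting and harms {22} stops event reporting at postoperative day 30.
- On the control arm, {6b} says: "Placebo was selected as a comparator".

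The two other places that describe the DSMB, Data management {19} and Composition of the data monitoring committee {21a}, give no alternative timetable. The former refers to separate DSMB Terms of Reference, which are not shown.

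**The concern.** The triggers read as if written for a trial of long-term treatment against usual care. Here treatment is over within a week and the control is placebo, so the conditions that would call the DSMB together describe something that does not happen.

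What is at stake is the timing of independent safety review. The article itself names hypotension, bradycardia, AV block, QT prolongation and ARDS as risks of the drug, says close monitoring is essential, and admits pneumonectomy patients, the group in which it reports ARDS with high-dose regimens. The DSMB may recommend interruption or termination, but its two scheduled occasions to do so depend on conditions that cannot be met. Adherence to safety and monitoring procedures is also one of the feasibility outcomes in Outcomes {12}, and adherence to an unworkable rule cannot be judged.

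**Working it through.** **Inputs**

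- Longest course: postoperative day 0 to day 5, 6 calendar days ({11a}).
- Follow-up and event reporting: 30 days ({14}, {22}).
- Triggers: 3 months (3 × 365.25/12 = 91.3 days) in 20 subjects, and 6 months (182.6 days) in all subjects ({21b}).
- Target: 80 randomised in 12 months ({14}). Minimum feasible enrolment: 1 per week ({12}).

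**Step 1: can the triggers be met?**

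| Trigger | Ratio to longest course | Ratio to follow-up | Patients who can meet it |
|---|---|---|---|
| 3 months of treatment | 91.3 / 6 = 15.2 | 91.3 / 30 = 3.0 | 0 of 80 (20 needed) |
| 6 months of treatment | 182.6 / 6 = 30.4 | 182.6 / 30 = 6.1 | 0 of 80 (all needed) |

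The mention of standard of care does not help. The randomised control is placebo on the same short schedule. Low-risk patients on standard care are not randomised and receive no study treatment.

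**Step 2: suppose the months mean time elapsed since treatment.** Assume even accrual at rate *r* per week and, for simplicity, treatment at randomisation. The 20th patient enters at week 20/*r*. The number randomised *w* weeks later is 20 + *r* × *w*, with *w* = 13 for 3 months and 30/7 = 4.29 for 30 days.

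| | *r* = 80/52 = 1.54 per week | *r* = 1 per week |
|---|---|---|
| 20th patient | week 13 | week 20 |
| Randomised at +3 months | 20 + 1.54 × 13 = 40 (week 26) | 20 + 13 = 33 (week 33) |
| Randomised at +30 days | 20 + 1.54 × 4.29 = 26.6 (week 17.3) | 20 + 4.29 = 24.3 (week 24.3) |
| Difference | 13.4 patients | 8.7 patients |

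As shares of 80, the 3-month reading gives 50% or 41% randomised at the first review, and the 30-day trigger gives 33% or 30%.

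Allocation is at the screening visit, before admission, so there is a gap between randomisation and treatment that the article does not state. A constant gap raises the +3-month and +30-day counts equally and leaves the differences of 13.4 and 8.7 unchanged.

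**Step 3: the last review.** Six months after the last treatment is 182.6 − 30 = 152.6 days, about 5 months, after the last patient's follow-up has ended.

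**The case against.** The strongest reply is that safety oversight does not depend on these two dates. The DSMB may meet whenever emerging results warrant it. Serious events related or possibly related to the intervention go to Health Canada within 7 or 15 days. There are discontinuation criteria for individual patients, and an internal monitoring visit is planned early in the trial. The unseen Terms of Reference may also hold a workable timetable. All of this is true, and it limits the point to the scheduled reviews: oversight is not absent. It does not remove the error. A discretionary review has no due date, event-by-event reporting is not a review of accumulated data by an independent board, and another document cannot make correct a schedule that the article states wrongly.

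Two further objections stand in part. The accrual figures rest on an assumed even rate and on the moment from which the clock runs, so they are best read as a range. Day 30 is also not the only workable anchor: a trigger at the end of the 6-day course would fall with about 21 patients randomised (20 + 1.54 × 6/7 = 21.3). As to the final review, on either timing it comes after all exposure has ended, so its delay affects the orderly close of the trial and not the protection of participants.

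The comparator wording alone would be minor, since both arms also receive standard postoperative care. It matters here because it sits inside the trigger and does not describe the randomised control.

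**Conclusion.** The concern holds and must be fixed. On the wording of {21b}, 0 of 80 patients can reach either trigger, so neither scheduled DSMB review can fall due. That conclusion needs no assumption beyond the article's own treatment and follow-up periods.

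On the lenient elapsed-time reading, the first review comes with about 33 to 40 patients randomised, against about 24 to 27 for a 30-day trigger. The 9 to 13 additional patients bring no later safety data on the first 20, because event reporting stops at day 30. These counts assume even accrual between 1 and 1.54 per week. No sample size, power or significance level depends on the point.

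**What to change.** In Interim analyses {21b}:

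- Set the first DSMB review when the first 20 randomised patients have reached postoperative day 30 or died.
- Set the final review when all randomised patients have completed 30-day follow-up.
- Keep the provision for additional reviews.
- Name the comparator as placebo.

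The 30-day anchor is recommended because it matches the follow-up and adverse event window already in the protocol, so the first review has complete safety data on those 20 patients. If the DSMB prefers an earlier anchor, such as the end of the treatment course, that also works, provided it is an event that patients actually reach.

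Check the DSMB Terms of Reference and give them the same wording. The cost is a text amendment to the protocol and, where needed, to the Terms of Reference. It adds no meetings or data collection and changes nothing in treatment.

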#### Methods for additional analyses (e.g., subgroup analyses) {20b}

Additional subgroup analysis by procedure type will be conducted.

#### Methods in analysis to handle protocol non-adherence and any statistical methods to handle missing data {20c}

The primary end point of this study is feasibility so no formal statistical analysis is planned. However, for the anticipated full-scale trial to follow, we plan to conduct analysis using an intention-to-treat, considering all patients as randomized regardless of whether they received the randomized treatment. Patients will be administered the intervention while admitted to hospital following major thoracic surgery so we anticipate very few patients to crossover or be lost to follow-up. To reduce the risk of missing data, we will capture data from patient health records, surveys, and manual chart review. Any departures from the protocol will be documented in the participant file and reviewed quantitatively to compare reasons. Reasons for missing data will be recorded, and multiple imputation methods will be used to address missing data in the analysis.

#### Plans to give access to the full protocol, participant-level data, and statistical code {31c}

There are no plans for granting public access to the full protocol, participant-level dataset, and statistical code beyond publication of this protocol.

#### Composition of the data monitoring committee, its role, and reporting structure {21a}

External oversight for this trial will be provided by an independent Data Safety and Monitoring Board (DSMB), consisting of one pharmacist and three clinician scientists. The DSMB will review matters related to the safety of study participants, validity and integrity of the data, enrollment rate relative to expectations, characteristics of participants, retention of participants, adherence to the protocol (potential or real protocol deviations), and data completeness.

#### Adverse event reporting and harms {22}

Amiodarone’s pharmacokinetic properties (namely its long half-life and prolonged washout period) as well the severe nature of some of its side effects make close monitoring essential among patients treated with this drug. Fortunately, many of the known adverse effects are secondary to tissue accumulation of amiodarone and are not seen with short-term therapy.

Below is a summary of how adverse events will be managed:
*Allergic reaction*: If there is appearance of an allergic reaction, the study drug will be stopped immediately. Symptoms of the allergic reaction will be managed with supportive measures including antihistamines and intra-muscular epinephrine, as appropriate.*Hypotension*: If hypotension occurs with reasonable clinical suspicion that it is secondary to the intervention, treatment will be withdrawn. Hypotension will be treated with fluid resuscitation and vasopressor therapy, as indicated.*Bradycardia/AV blockade*: If bradycardia or AV blockade occurs with reasonable clinical suspicion that it is secondary to the intervention, treatment will be withdrawn. Severe bradycardia may require pharmacological treatment with atropine, dopamine, or epinephrine, or may require transcutaneous pacing. Our cardiology service will be consulted to assist with management as necessary.*ARDS*: If ARDS occurs (as defined under the Berlin definition), treatment will be withdrawn. ARDS will be managed according to standard of care with supportive treatments. Our respirology and/or intensive care teams will be consulted as needed to assist with management.*QT prolongation:* If QTc interval is prolonged with reasonable clinical suspicion that it is secondary to the intervention, treatment will be withdrawn. Any electrolyte abnormalities that would predispose the patient to cardiac arrhythmia will be corrected. Development of any ventricular arrhythmias will be managed in accordance with standard of care. Our cardiology service will be consulted to assist with management as necessary.

In the event of development of a significant adverse event, clinical follow-up will be arranged as necessary with our cardiology service.

Any events that occur after the patient starts the study intervention will be reported until postoperative day 30. All adverse events will be collected using the Common Terminology Criteria for Adverse Events (version 5.0) and reported on the applicable case report form [24]. All events will also be entered in an adverse event tracking log. Adverse events which are serious and unexpected, related or possibly related to the intervention, will be reported to the REB according to local requirements. Serious AEs (SAE) will be reported to Health Canada. If an event is determined to be serious, and related or possibly related to the intervention, regardless of expectedness, the Sponsor Investigator will notify Health Canada as soon as possible but no later than 7 calendar days after becoming aware of the event for fatal or life-threatening events, and no later than 15 days after becoming aware for non-fatal/life threatening events. Medical and scientific judgment will be exercised in deciding whether expedited reporting is appropriate in other situations.

#### Frequency and plans for auditing trial conduct {23}

The Ottawa Hospital Research Institute Internal Monitor will conduct a monitoring visit early on in the trial.

#### Plans for communicating important protocol amendments to relevant parties (e.g., trial participants, ethical committees) {25}

All protocol amendments will be reviewed and approved by the REB for prior approval or notification. The Principle Investigator will sign and date the approved protocol amendment prior to implementation. Any departures from the protocol will be documented in the participant file.

### Dissemination plans {31a}

The trial results will be disseminated to the public and to relevant clinical and academic communities. This will be done through submission for publication in an academic journal, through conference presentations, and to thoracic surgery patients via outreach to patient advocate groups and societies.

## Trial status

This manuscript reflects the protocol version 4. The funding body has no role in the design of the study; in the collection, analysis, and interpretation of data; and in writing the manuscript dated May 19, 2020. Recruitment is anticipated for June 2021 and anticipated to be complete June 2022.

## Data Availability

Only the investigator team will have access to the final trial dataset.

## Abbreviations

AE: Adverse events
ARDS: Adult respiratory distress syndrome
DMP: Data Management Plan
DSMB: Data Safety Management Board
POAF: Postoperative atrial fibrillation
REB: Research Ethics Board
SAE: Serious adverse events
TM&M: Thoracic Morbidity And Mortality
